## Abstract

**Background:**

Congenital diaphragmatic hernia (CDH) is a severe congenital anomaly of the diaphragm resulting in pulmonary hypoplasia and pulmonary hypertension. It is associated with a high risk of mortality and pulmonary morbidity. Previous retrospective studies have reported high frequency oscillatory ventilation (HFO) to reduce pulmonary morbidity in infants with CDH, while others indicated HFO to be associated with worse outcome. We therefore aimed to develop a randomized controlled trial to compare initial ventilatory treatment with high-frequency oscillation and conventional ventilation in infants with CDH.

**Methods/design:**

This trial is designed as a multicentre trial in which 400 infants (200 in each arm) will be included. Primary outcome measures are BPD, described as oxygen dependency by day 28 according to the definition of Jobe and Bancalari, and/or mortality by day 28. All liveborn infants with CDH born at a gestational age of over 34 weeks and no other severe congenital anomalies are eligible for inclusion. Parental informed consent is asked antenatally and the allocated ventilation mode starts within two hours after birth. Laboratory samples of blood, urine and tracheal aspirate are taken at the first day of life, day 3, day 7, day 14 and day 28 to evaluate laboratory markers for ventilator-induced lung injury and pulmonary hypertension.

**Discussion:**

To date, randomized clinical trials are lacking in the field of CDH. The VICI-trial, as the first randomized clinical trial in the field of CDH, may provide further insight in ventilation strategies in CDH patient. This may hopefully prevent mortality and morbidity.

**Trial registration:**

Netherlands Trial Register (NTR): NTR1310

## Background

Congenital diaphragmatic hernia (CDH) is a severe congenital anomaly of the diaphragm, which occurs in approximately one in 3000 live births [1]. In CDH, the diaphragmatic defect allows abdominal organs to herniate into the chest cavity. As a consequence, underdevelopment of the lungs and abnormal pulmonary vasculature growth may occur, resulting in pulmonary hypoplasia and pulmonary hypertension [2,3].

Children with CDH mostly present with immediate cardiorespiratory distress during the first hours of life. The initial therapy for these children is mechanical ventilation and cardiorespiratory stabilization in support of optimal management of the pulmonary hypoplasia and pulmonary hypertension [4]. Thereafter, surgical repair of the diaphragmatic defect is indicated [4]. Although many advances in treatment for CDH patients have been made throughout the years, CDH remains a life-threatening condition with a reported mortality of 20-70%, depending on case selection [5].

Survivors of CDH are at risk of developing secondary morbidity, such as gastro-intestinal, neurodevelopmental and pulmonary sequelae. Throughout infancy and childhood, a broad spectrum of pulmonary morbidity may occur, such as bronchopulmonary dysplasia (BPD), persistent pulmonary hypertension, recurrent respiratory tract infections and asthmatic symptoms [6]. BPD is characterized by disturbances of the normal alveolarization. Ventilator-induced lung injury, oxygen toxicity, pulmonary inflammatory responses, and severe pulmonary hypertension predispose infants with CDH to develop BPD [7,8]. A recent report of the CDH Registry reported the prevalence of BPD to be 41% in infants with CDH [9]. About half of the CDH survivors with BPD are reported to have moderate to severe BPD [10]. Moreover, lung function anomalies are often present in these patients [11-14].

Optimizing ventilation strategies in patients with CDH may help to prevent chronic respiratory disease. However, evidence-based standardized treatment protocols based are lacking in the field of CDH. Consequently, ventilation strategies may differ between centres and ventilatory support is often based upon expert opinion [7]. To date, conventional ventilation is the most widely used initial ventilation mode in newborns with CDH, while in many institutions high frequency oscillatory ventilation (HFO) is used as rescue therapy. In some centres, however, HFO is used as the initial ventilation mode.

HFO achieves adequate gas exchange by an oscillatory pump, which combines very high respiratory rates and low tidal volumes. HFO may improve gas exchange, promote uniform lung inflation, reduce barotrauma, and decrease the presence of inflammatory mediators [7,15-18]. HFO has been used in preterm infants with respiratory distress syndrome, either as an elective ventilation strategy or as a rescue therapy [16]. A Cochrane review, on the use of elective HFO compared to CMV in preterm infants, found a borderline significant reduction in the rate of chronic lung disease with the use of HFO [16]. A second Cochrane review described the use of HFO as a rescue therapy in term and near term infants with severe pulmonary dysfunction. Only one trial compared these two ventilation strategies prospectively, resulting in no significant difference in outcome, need for extracorporeal membrane oxygenation (ECMO), or complications [15,19].

In infants with CDH, retrospective and observational studies reported improved survival and a lower incidence of chronic lung disease with elective use of HFO [20-25]. HFO was reported to provide better oxygenation and higher MAP without increasing the incidence of barotraumas [20,21]. In one study, the use of HFO avoided hyperventilation as well as the need for ECMO [17]. Moreover, inhaled nitric oxide was documented to result in better gas exchange following recruitment of the lungs by HFO [26]. On the contrary, HFO may cause lung hyperinflation in some patients, which may induce higher alveolar and mean airway pressures [21]. This may result in an increased risk of pulmonary barotrauma and hemodynamic instability [21]. A recent study by the CDH Registry reported HFO as initial ventilation mode to be associated with an increased rate of mortality and BPD [9]. In this study, it is speculated that infants who received initially HFO were more severely ill from the start [9].

Conclusively, chronic pulmonary morbidity and high mortality rates are major problems in infants with CDH. Several retrospective and observational studies have reported that mechanical ventilation strategies may have an impact on outcome and pulmonary morbidity in CDH patients. Therefore, we aimed to develop a randomized controlled trial to compare initial ventilatory treatment with HFO and conventional ventilation in infants with CDH. The acronym VICI is deducted from the words: HFO versus conventional **V**entilation in **I**nfants with **C**ongenital diaphragmatic hernia: an **I**nternational randomised clinical trial. In Latin vici means 'I have conquered' which refers to our patients with CDH which are very vulnerable and ill and sometimes have to struggle to survive.

The primary objective of this trial is to determine if there is a difference in the incidence of BPD and/or death within the first 28 days of life between newborns with congenital diaphragmatic hernia treated with high frequency oscillatory ventilation (HFO) and those treated with conventional mechanical ventilation (CMV) as initial ventilation mode. Secondarily, we also aim to compare the severity of BPD, ventilator-induced lung injury and pulmonary hypertension by using clinical and laboratory parameters.

## Methods/Design

This study is designed as a prospective, randomized controlled multicentre trial. All participating centres are member of the CDH-EURO Consortium. This is a collaboration between European tertiary centres, who have an expertise in the field of CDH. The CDH-EURO consortium was started in 2006 and aims at cooperation between centres, enhancement of research in the field of CDH and development of standardized evidence-based treatment protocols.

### Outcome measures

The primary outcome measure is BPD and/or death within the first 28 days of life. Secondary outcome parameters are overall mortality, severity of BPD, number of days on the ventilator, number of treatment failures, ventilation-induced lung injury and pulmonary hypertension according to clinical and laboratory parameters and need for ECMO (only for ECMO centres). BPD is defined as oxygen dependency at day 28, according to the definition of Jobe and Bancalari [27]. The severity of BPD is also defined according to this definition (see table 1).

**Table 1 T1:** definition of BPD according to Jobe and Bancalari

Gestational age	< 32 weeks	> 32 weeks
**Time point assessment**	36 wks PMA* or DC** to home, whichever comes first	> 28 days but < 56 days of life or discharge to home, whichever comes first
**Treatment with oxygen > 21% for at least 28 days PLUS**		
**Mild BPD**	On room air at 36 wks PMA or at DC, whichever comes first	On room air at day 56 postnatal age or DC, whichever comes first
**Moderate BPD**	< 30% O2 at 36 wks PMA or DC, whichever comes first	< 30% O2 at 56 d of life or DC whichever comes first
**Severe BPD**	≥ 30% O2 and/or pos. pressure at 36 wks PMA or DC whichever comes first	≥ 30% O2 and/or pos. pressure at 56 d of life or DC whichever comes first

*PMA = post-menstrual age

**DC = discharge

### Inclusion and exclusion criteria

The study population consists of all infants antenatally diagnosed with CDH born at one of the participating centres.

Exclusion criteria are:

• Birth before a gestational age of 34 weeks

• Severe chromosomal anomalies, like trisomy 18 or trisomy 13, which may imply a decision to stop or not to start life-saving medical treatment

• Severe cardiac anomalies, expected to need corrective surgery in the first 60 days of life (such as transposition of the great arteries, truncus arteriosus or double outlet right ventricle)

• Renal anomalies associated with oligohydramnios

• Severe orthopaedic and skeletal deformities, which are likely to influence thoracic, and/or lung development (such as chest wall deformities and spine anomalies)

• Severe anomalies of the central nervous system

### Statistical analysis

We estimated that a total of 400 newborns can be included within a period of three years. In a previous study of the CDH study group, the incidence of BPD and/or death within the first 28 days of life is reported to be about 50% [9]. Assuming a difference of 15% in BPD and/or death within the first 28 days between both treatment groups, 186 patients are required per arm for a power of 80% at two-sided alpha is 0.05. To allow for some non-evaluable patients and dropouts, 200 patients per group will be included. To achieve equal distribution of the two ventilation modes among the participants, block randomization stratified per centre will be carried out. The data-analysis will be carried out at the Erasmus MC, Rotterdam. An intention-to-treat analysis will be performed. A p-value (two-sided) < 0.05 will be considered significant in all analyses.

The primary endpoint will be evaluated using multiple logistic regression analysis taking account of: centre, lung-to-head ratio, position of the liver (intra-abdominal or intra-thoracic) and the side of the defect (left, right or central). A subgroup analysis will be carried out in operated infants to evaluate the defect size, according to the CDH study group defect size scale (http://www.cdhsg.net).

The secondary endpoints will be evaluated by using the following statistical tests. Overall mortality in the first year of life will be analysed by Kaplan-Meier curves and Log rank tests. The chi-square test will be used to analyse number of treatment failures, presence of pulmonary hypertension according to echocardiographic parameters, requirement of medication at discharge and during the first year of life, and need for ECMO therapy (in ECMO centres). The Mann-Whitney test is used to evaluate the severity of chronic lung disease, number of days on the ventilator and the fraction of days with required medical treatment for pulmonary hypertension during the hospital admission. In the evaluation of the severity of chronic lung disease and the number of days on the ventilator, deaths are counted as worst outcome according to the intention-to-treat principle. Repeated measures ANOVA is used to evaluate levels of laboratory markers for ventilator-induced lung injury or pulmonary hypertension and pulmonary function at the age of six and twelve months. This analysis allows for missing data at different time points and is considered as the optimal way for evaluation of longitudinal data.

All the above-mentioned analyses will allow for centre by stratification.

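### The secondary endpoints are tested with centre as the only baseline factor; adding the other three primary-model covariates could gain power, by an amount the documents cannot fix

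*Protocol article*

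**What the plan says.** All of this is in the Statistical analysis section of the protocol article.

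- **Primary endpoint** (BPD and/or death by day 28): "multiple logistic regression analysis taking account of: centre, lung-to-head ratio, position of the liver", and also the side of the defect.
- **One-year mortality:** "Overall mortality in the first year of life will be analysed by Kaplan-Meier curves and Log rank tests".
- **Other secondary endpoints:** chi-square tests for treatment failure, echocardiographic pulmonary hypertension, medication and ECMO; Mann-Whitney tests for severity of chronic lung disease and ventilator days (with death ranked worst) and for the share of days on pulmonary hypertension treatment. No covariate is named for any of these.
- **Centre:** "All the above-mentioned analyses will allow for centre by stratification". Centre is also the only randomisation stratum.
- **Significance level:** "A p-value (two-sided) < 0.05 will be considered significant in all analyses".

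The section states power for the primary endpoint only.

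**The concern.** Death is one half of the primary composite. Factors chosen to explain BPD or death at 28 days are natural candidates to explain one-year death, BPD severity and ventilator days. The article includes them in the primary model and drops them, without a reason, from the endpoints that will be read beside it. The choice is stated, so it is not a detail left to an unseen analysis plan.

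Two features make the omission worth raising. First, randomisation balances lung-to-head ratio, liver position and side only by chance. Second, the Background section reports the speculation that infants started on HFO in the registry were sicker from the outset, so the authors themselves regard baseline severity as important in this comparison.

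What is at stake is power. A log-rank test loses power when strong prognostic factors are left out of it, and one-year mortality is likely to have limited power to begin with.

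**Working it through.** **1. The plan's own figure.** The documents give no power for any secondary endpoint, so only the primary sample size can be reproduced. The inputs are a reference rate of about 50%, a 15-point difference, 80% power and two-sided alpha 0.05. The article says "186 patients are required per arm for a power of 80% at two-sided alpha is 0.05".

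For 50% vs 35%, with pooled variance:

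n = [1.96·√(2·0.425·0.575) + 0.8416·√(0.5·0.5 + 0.35·0.65)]² / 0.15² = (1.370 + 0.582)² / 0.0225 ≈ 169.3, so 170 per arm.

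With continuity correction: n' = (n/4)·[1 + √(1 + 4/(n·0.15))]² ≈ 182.4, so 183 per arm. This is within 3% of 186. The stated size is not in dispute.

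**2. Inputs for one-year mortality.**

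From the documents: 400 infants allocated 1:1, two-sided alpha 0.05, a log-rank test stratified by centre, and the three omitted covariates.

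Assumed, because the documents do not give them:

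- Control-arm one-year mortality of 20% or 30%. The Background cites 20-70% by case selection, with no time point.
- Hazard ratio 0.6, conditional on the covariates.
- Ten centres of 40 infants, with a centre SD of 0.3 on the log hazard.
- Lung-to-head ratio standard normal; liver position correlated with it; 15% with the less common side.
- Exponential survival, censored at one year.
- Log hazard ratios per SD lower lung-to-head ratio, for liver position and for side: 0, 0, 0 (none); 0.4, 0.5, 0.3 (moderate); 0.8, 0.9, 0.5 (strong).

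**3. Analytic cross-check without prognostic covariates.** Events = 200·[m + 1 − (1 − m)^0.6], and power = Φ(√(events/4)·|ln 0.6| − 1.96).

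- m = 0.20: events = 200·(0.200 + 0.125) ≈ 65; power = Φ(4.03·0.511 − 1.96) ≈ 54%.
- m = 0.30: events = 200·(0.300 + 0.193) ≈ 99; power = Φ(4.96·0.511 − 1.96) ≈ 72%.

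**4. Simulation.** There were 1,500 trials per scenario, with each analysis applied to the same simulated trials. Monte Carlo error is about √(0.5·0.5/1500) = 1.3 points.

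| Control mortality | Covariates | Centre-stratified log-rank (plan) | Centre-stratified Cox + 3 covariates | Change |
|---|---|---|---|---|
| 20% | not prognostic | 51.5% | 50.4% | −1.1 |
| 20% | moderate | 52.5% | 54.1% | +1.6 |
| 20% | strong | 44.5% | 52.8% | +8.3 |
| 30% | not prognostic | 70.9% | 70.3% | −0.6 |
| 30% | moderate | 66.1% | 70.5% | +4.4 |
| 30% | strong | 57.5% | 71.5% | +14.0 |

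The rows without prognostic covariates agree with step 3. The adjusted column stays at 50-54% and 70-72% whatever the prognostic strength. With strongly prognostic covariates the planned test falls well below it.

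**5. Validity.** With a true hazard ratio of 1, rejection rates lay between 4.0% and 5.9% for both analyses in every scenario.

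No power was computed for the chi-square or Mann-Whitney endpoints.

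**The case against.** The strongest reply is that nothing here is an error. Centre-stratified log-rank, chi-square and Mann-Whitney tests are conventional, they respect the randomisation stratum, and they hold their type I error. The plan sets no power target for secondary endpoints, so none is missed. Primary and secondary endpoints may properly have different adjustment sets. All of this stands, and it makes the point one of efficiency.

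Four stronger readings are tempting, and the documents do not support them.

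- *The secondary results would be biased by chance imbalance.* The 5% error rate already allows for chance imbalance under randomisation. Adjustment adds precision; it does not repair an invalid test.
- *None of the primary model's factors is carried over.* Centre is, in every analysis.
- *The loss is certainly large.* No prognostic strength is given. Gains well above 14 points need very strong prediction. For example, a baseline score with a log hazard ratio of 1.3 per SD, at 30% overall mortality, implies one-year risks of about 4% at its 10th centile and 72% at its 90th. Nothing in the article shows that three antenatal variables predict that well.
- *Adjustment is free because the values exist for every infant.* The article does not say that lung-to-head ratio is available for all, and the models bring assumptions of their own.

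It may also be said that effect estimates and supportive models belong in the analysis plan. That is fair for estimates and confidence intervals, and their absence is no part of this point. It does not reach the choice of tests, which the article fixes itself.

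**Conclusion.** The point holds as a modest improvement in efficiency. The article commits the secondary endpoints to tests that use centre but omit lung-to-head ratio, liver position and side of defect, all of which the primary model needs anyway.

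For one-year mortality, the gain from adding them runs from about nil (the −1 to −0.6 points seen with non-prognostic covariates are within simulation error) through +2 to +4 points to +8 to +14 points. It depends on prognostic strength that has to be assumed, as do the hazard ratio of 0.6 and the control-arm mortality of 20-30%. The asymmetry supports the change: little is lost if the covariates turn out uninformative, and a useful amount is gained if they are as prognostic as their place in the primary model suggests.

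The same reasoning carries to the other secondary endpoints in direction, because the Mann-Whitney and log-rank tests are in essence score tests of the ordinal and Cox models without covariates. The size there has not been calculated.

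**What to change.** Before any unblinded analysis:

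- Keep the Kaplan-Meier plot. Test one-year mortality with a Cox model stratified by centre that includes lung-to-head ratio, liver position and side of defect.
- Use logistic models with the same covariates, allowing for centre, for the binary endpoints. Keep ECMO restricted to ECMO centres, as planned.
- Use ordinal models with the same covariates, allowing for centre, for BPD severity and ventilator days, with death as the worst category.
- Report hazard or odds ratios with 95% confidence intervals.
- Keep infants with missing lung-to-head ratio in every adjusted model, by simple imputation or a missing-indicator.
- Retain the planned centre-stratified tests as sensitivity analyses.

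The change needs no alteration to sample size or conduct, and no covariate beyond those the primary model already requires. Its costs are effect estimates that are conditional on the covariates, proportional-hazards and proportional-odds assumptions, and a rule for missing covariates. The primary model already faces the last of these.

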### Study procedures

Parental informed consent will be obtained antenatally to enhance quick randomization. Following antenatal diagnosis, the parents are to be counselled and will receive information about the study, including a patient information letter and an informed consent form. If both parents decide to participate in the study, as soon as possible after birth central randomization will take place by the treating physician using a website. This way concealed allocation is guaranteed. Within two hours after delivery, the allocated ventilatory treatment has to be started.

The patient receives the allocated ventilation treatment during the entire admission period on the intensive care unit. During surgery, the child preferably remains on the allocated ventilation type, provided the treating surgeon agrees. Should the surgeon opt for the other ventilation mode, the patient is switched to the allocated ventilation treatment again after surgery. If the patient has to be re-intubated within the first 60 days after the start of the allocated treatment, the patient receives the allocated treatment again. Patients are observed up to day 60 after birth or until discharge whichever comes first. In Figure 1, an overview of the study procedures is given.

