### Standardized treatment and ventilation settings

All infants participating in the VICI-trial are treated according to the same standardized treatment protocol which has been published recently [4]. This protocol of standard practice was decided upon available evidence and consensus between the participating centres.

After birth, all infants are immediately intubated. In general, our goals are to achieve preductal saturations between 85 and 95%, postductal saturation levels above 70% and arterial CO_2 _levels between 45-60 mm Hg (permissive hypercapnia). Conventional mechanical ventilation is provided by a neonatal ventilator capable of positive pressure ventilation or triggered modes (Babylog ventilator, Dräger Medical, Germany). High frequency oscillatory ventilation (HFO) is provided by a high frequency oscillatory ventilator (Sensormedics 3100A/B HFO Ventilator, Viasys Healthcare, USA).

If the allocated treatment is conventional ventilation, the following settings are used: a peak inspiratory pressure (PIP) of 20-25 cm H_2_O, a positive end-expiratory pressure (PEEP) of 2-5 cm H_2_O and a frequency of 40-60 per minute. In case of HFO, the settings are: a mean airway pressure (MAP) of 13 to 17 cm H_2_O, a frequency of 10 Hz, an amplitude (Δp, cm H_2_O) of 30 to 50 obtaining chest vibrations, and an inspiration/expiration rate (I:E) of 1:1.

According to our standardized treatment protocol, a chest radiograph is made as soon as possible after birth to assess the initial condition and is repeated guided on the patient's condition. In case of HFOV, a chest radiograph is also made after this ventilation mode is started to confirm that the lungs are not overinflated, as defined by a contralateral lung expansion of over 8 ribs. Also, echocardiography is performed within the first 24 hours after birth to assess pulmonary arterial diameter and right heart function. In all patients, a chest radiograph and echocardiography are repeated at day 28.

Weaning from conventional ventilation is done by means of decreasing PIP. Frequency and/or the PIP-PEEP were modified to achieve PaCO_2 _levels above 45 mmHg. In case of HFOV, Δp was decreased if the paCO_2 _was below 45 mmHg and FiO_2 _was decreased if preductal saturation levels were above 95%.

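### Deaths are ranked worst for two of the three Mann-Whitney endpoints but not for the fraction of admission days on pulmonary-hypertension treatment, whose denominator death and length of stay both change

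*Protocol article*

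**What the plan says.** All references are to the protocol article.

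- **Statistical analysis, Mann-Whitney endpoints.** One sentence assigns the test to three endpoints: severity of chronic lung disease, days on the ventilator, and "the fraction of days with required medical treatment for pulmonary hypertension during the hospital admission". The next sentence covers deaths and cites intention to treat as its reason, but names only the first two: "In the evaluation of the severity of chronic lung disease and the number of days on the ventilator, deaths are counted as worst outcome".
- **Statistical analysis, chi-square endpoints.** These include "presence of pulmonary hypertension according to echocardiographic parameters, requirement of medication at discharge and during the first year of life". No rule for deaths is stated for them.
- **Analysis set.** "An intention-to-treat analysis will be performed".
- **Standardized treatment and ventilation settings.** Echocardiography is done within 24 hours of birth, and then "In all patients, a chest radiograph and echocardiography are repeated at day 28".
- **Study procedures.** "Patients are observed up to day 60 after birth or until discharge whichever comes first".
- **Background.** "CDH remains a life-threatening condition with a reported mortality of 20-70%, depending on case selection".

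No other section gives a rule for deaths for the pulmonary-hypertension or medication endpoints.

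**The concern.** The authors saw that an infant who dies early spends few days on the ventilator and never reaches the assessment of lung disease severity, so that leaving deaths alone would flatter the arm with more of them. They closed that gap for two endpoints. The third endpoint in the same sentence is exposed to the same problem and to a further one.

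A fraction of admission days has a denominator fixed after randomisation. Death shortens the admission, and so may a better ventilation mode. The fraction can move although the burden of pulmonary hypertension has not, and the score given to an infant who dies depends on how much of a short life was spent on treatment. With reported mortality of 20-70%, deaths are too many to ignore.

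At stake is a secondary result that could be significant at the 5% level in either direction for reasons unrelated to pulmonary hypertension, and could be read as evidence for or against a ventilation mode.

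**Working it through.** The article gives no figure for this endpoint, so there is none to reproduce. The only design number used is 200 infants per group. Mortality of 20% or 30% lies within the quoted range or at its edge. Lengths of stay, treated days and event rates are assumptions.

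**1. The fraction as defined.** Score = treated days / admission days.

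| Infant | Calculation | Score |
|---|---|---|
| 10 treated days, 20-day stay | 10/20 | 0.50 |
| 10 treated days, 40-day stay | 10/40 | 0.25 |
| Dies on day 2, never treated | 0/2 | 0 (best possible) |
| Dies on day 3, treated every day | 3/3 | 1 (worst possible) |

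**2. Effect of how deaths score.** Simulation with 200 per arm, the same distributions of stay and treated days in both arms, mortality 30% versus 20% unrelated to treated days, and an unstratified two-sided Mann-Whitney test at 0.05:

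- Deaths score 1: the deadlier arm is significantly worse in about 34-40% of trials.
- Deaths score 0: the deadlier arm is significantly better in about 38-43% of trials.

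Other assumed treatment patterns widen these ranges to 36-46% and 25-46%. The nominal rate in one direction is 2.5%. Real deaths would fall between the two extremes, so the text does not fix the direction.

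**3. If the sickest infants die.** A second simulation made the deaths the most severe cases, with no effect of ventilation mode on pulmonary hypertension. The deadlier arm (30% versus 20%) was significantly better in about 42% of trials with survivors only and 62% with deaths set to 0. It was significantly better in 0% with deaths ranked worst, and also in 0% if every infant who died had been treated on all days until death.

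**4. Effect of length of stay alone.** With equal mortality of 20% and median stays of 30 versus 40 days, the test rejects in 35-79% of trials if treated days are independent of stay, depending on the shape assumed for treated days. If treated days are proportional to stay, it rejects in about 4-6%, close to the nominal 5%. Under the severity model of step 3, stays 30% longer make the longer-stay arm significantly better in about 13% of trials.

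**5. Endpoints seen only in survivors** (day-28 echocardiogram, medication at discharge). Take 200 per arm and deaths of 20% in A and 30% in B, that is 40 and 60. Assume 35% of A's survivors have the event: 0.35 × 160 = 56.

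| B's 20 extra deaths | Survivors only, A vs B | Death or event, A vs B |
|---|---|---|
| All among infants who would have had the event | 56/160 = 35.0% vs 36/140 = 25.7% (p=0.08) | 96/200 = 48.0% vs 96/200 = 48.0% |
| Unrelated to the event | 56/160 = 35.0% vs 49/140 = 35.0% | 96/200 = 48.0% vs 109/200 = 54.5% (p=0.19) |

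In the first row, deaths of 20% versus 25% give 35.0% versus 30.7% among survivors (p=0.42), and deaths of 20% versus 35% give 35.0% versus 20.0% (p=0.005). Survivors-only figures mislead when the extra deaths are related to pulmonary hypertension, and not otherwise.

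**The case against.** The strongest reply is that a condensed article may leave the handling of deaths to an analysis plan that is not shown. For the chi-square endpoints this largely stands: the article states no rule, and silence is not an error. It does not stand for the fraction. There the article itself writes the denominator, and itself states a rule for deaths that skips one of the three endpoints just listed.

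The second reply is that the size depends on the inputs. This stands. The stay effect disappears if treated days scale with stay, and an infant treated on every day until death already has the worst score.

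Four stronger readings are tempting, and the document supports none of them:

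- *A mode that saves sick infants would appear to cause pulmonary hypertension.* It could. For the fraction, the direction turns on how deaths score. For the survivor endpoints, it turns on which infants die.
- *These comparisons are not intention-to-treat.* The article keeps infants in their allocated group, including those who switch mode or receive ECMO. Truncation by death concerns what is being estimated, not departure from allocation.
- *All pulmonary-hypertension and medication endpoints exist only for survivors.* An echocardiogram is also done within 24 hours, the article does not say which one defines the endpoint, and medication in the first year can be recorded for infants who die during that year.
- *Deaths without ECMO or treatment failure count as successes.* Both endpoints can be counted in all randomised infants (ECMO in ECMO centres). Failure is defined by physiological criteria that many dying infants would plausibly meet, and a death without ECMO is correctly a case without ECMO.

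**Conclusion.** The point holds for the fraction of admission days on pulmonary-hypertension treatment. Followed as written, that comparison can favour the arm with more deaths or longer stays, and the article does not fix how an infant who dies is scored. The possible distortion is large under the assumed mortality of 30% versus 20%, but its direction cannot be stated in advance. No percentage above is a prediction for this trial.

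For day-28 echocardiography and medication at discharge the point is narrower: survivors-only results may mislead if the extra deaths are among infants with pulmonary hypertension. ECMO and treatment failure are not affected.

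This is a change that should be made, not one on which the trial depends. The primary endpoint includes death, overall mortality has its own analysis, and neither is touched.

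**What to change.** 1. Add the pulmonary-hypertension treatment endpoint to the sentence that ranks deaths as worst outcome.
2. Analyse it as days alive and free of pulmonary-hypertension treatment over a fixed window, with deaths ranked worst, by a Mann-Whitney test stratified by centre (the plan already stratifies its analyses by centre). Use day 28, or day 60 if treatment after discharge is recorded. Keep the fraction as a descriptive figure.
3. For day-28 echocardiographic pulmonary hypertension and medication at discharge, report death or event in all randomised infants beside the survivors-only figures, and tabulate the components. State which echocardiogram defines the endpoint.
4. Leave ECMO and treatment failure as they are.

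The cost is mainly analysis wording. Two cautions apply. Observation stops at day 60 or discharge, whichever is first, so a window that runs past discharge needs treatment status from then on. The ranked measure and the combined endpoints are also partly driven by death and overlap with the mortality analysis, which is why the components must be shown.
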